Outcome assessments include intervention attendance rates, self-report measures of intervention satisfaction, pain, fatigue, sleep quality, psychological distress, mindfulness, a 6 min walk test measuring functional capacity, and treatment expectations. Assessments will be completed at baseline, post-treatment, and 3-month and 6-month follow-up. In addition, during the intervention period, participants will complete brief daily diaries on alternate weeks (4 weeks total) assessing symptoms (pain, fatigue, positive mood, negative mood, pain catastrophizing, pain acceptance) and yoga practice. An innovative feature of this study is that we will utilize these daily measures to conduct a rigorous test of two key psychological mediators that may explain the mechanisms of treatment effects. Pain theory and research point to two variables—pain catastrophizing (the tendency to focus on and exaggerate the threat value of painful stimuli and negatively evaluate one’s own ability to deal with pain) and pain acceptance (the willingness to experience pain and yet remain engaged in meaningful life activities despite pain)—that are likely to be particularly important in explaining the effects of the yoga intervention on pain and pain-related outcomes [38, 39]. Understanding the underlying mechanisms of the yoga intervention’s potential effects could have far-reaching implications for the design and evaluation of future yoga interventions for conditions entailing persistent pain.

The setting of the study is an urban tertiary care academic medical center located in Durham, North Carolina (Duke Cancer Institute). This study has been reviewed and approved by the Duke Medical Center Institutional Review Board (IRB). The study will adhere to the CONSORT guidelines for clinical trials [34]. The study flow is presented in Fig. 1.

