### Adherence and retention strategies

Adherence and retention are crucial determinants of the quality and interpretability of clinical trials. Obstacles to treatment attendance when intervening with patients with advanced disease include a variety of illness-related issues, such as unpredictable worsening of symptoms, limited energy, and alternate patient priorities given shortened life expectancies. Strategies we have implemented to boost attendance are among the best practices used in many high quality behavioral intervention trials. These strategies include motivational interviewing during the recruitment phase, weekly reminder emails during the intervention phase, prompt calls from interventionists to participants who missed a class, and make up sessions. Adequate adherence in this trial has been defined as 70% of the participants attending full sessions (120 min each) for at least 4 of the 8 treatment sessions. This is a revision from the initial definition of adequate adherence, which specified 70% attendance of at least 7 intervention sessions. We believe that the revision represents a more reasonable expectation given the severity of illness in this patient population. In reviewing data from three previous studies of the 8-session Mindful Yoga intervention, it was apparent that the goal of 70% of participants attending at least 7 sessions was likely overly ambitious [32, 33, 44]. This was achieved in only one of the three previous studies, with a population of much healthier women who were post-treatment for early stage breast cancer [32].

Attrition is a recognized challenge in studying the MBC population, given the progressive nature of the disease. To minimize missing data, we developed a retention plan to ensure minimal dropout due to reasons other than death or severe disease progression. This plan has featured minimization of participant burden, provision of participant support through the intervention protocols, solicitation of information about participant difficulties and prompt response to concerns raised, and consistent efforts to optimize the participants’ experience of study participation. Continuous quality monitoring of retention key performance indicators has allowed us to rapidly identify and respond to problems.

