### Statistical analysis

The primary outcome related to feasibility is attendance, which is measured weekly at each intervention session. Adequate feasibility will be indicated by at least 70% of patients attending ≥ 4 of 8 sessions. The primary outcome related to acceptability is quantified by the Client Satisfaction Questionnaire-8 as assessed at the post-intervention evaluation. Adequate acceptability of the yoga intervention will be indicated by ≥ 80% of participants reporting a mean satisfaction score ≥ 3. Secondary outcomes are measurements of change at the post-treatment, 3-month follow-up, and 6-month follow-up evaluations in pain, fatigue, sleep quality, psychological distress, mindfulness and functional capacity. These will be analyzed both as individual time points and in longitudinal analyses. Treatment expectations—including potential pre-randomization selection biases regarding the yoga intervention—will be controlled in analyses with the data from the measure assessing outcomes expectations [66]. We will apply the intent-to-treat assumption for all analyses.

We will also explore within-person associations between yoga practice, outcomes (pain, fatigue, mood) and mediators (pain catastrophizing, pain acceptance) among participants in the yoga condition. Multilevel random effects models will be used to evaluate these associations, with individuals’ mean levels of yoga practice as a control variable, and practice rates person-centered to control for potentially spurious within-person associations [67]. Multilevel modeling is an advanced methodology for integrating data from multiple levels of sampling, such as this study’s two levels (within-persons and between-persons). Multilevel models are particularly advantageous in analyzing data sets with many repeated measures, such as daily diary records [68, 69]. By preserving the rich detail in each individual’s full data set, multilevel models allow for a sensitive independent determination of day-to-day interrelated happenings for each patient, as well as aggregation of individual estimates for reliable results for the average patient. Multilevel models also enable strict control for potential confounds, such as serial autocorrelation in measurements.

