## Discussion

In this report we have summarized the challenges of designing a randomized controlled trial of a yoga intervention for metastatic breast cancer patients with long-term follow-up. The challenges we faced in this design included ensuring adequate recruitment including of minorities, limiting and controlling for selection bias, tailoring of the yoga intervention, and maximizing adherence and retention. This project will provide important information regarding the feasibility and acceptability of yoga as an intervention for women with advanced cancer, and valuable preliminary data on the psychological and functional effects of yoga for MBC patients, including the first systematic evaluation of the psychological mechanisms by which a yoga intervention may produce pain relief. This investigation will also establish rigorous methods for future research for testing the mechanisms by which yoga may affect pain, fatigue, emotional distress, and functional capacity in this population.

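### Person-centring practice cannot control spurious within-person associations in the daily-diary models, so the same-day associations cannot carry the mediator and mechanism claims

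*Protocol article*

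**What the plan says.** The protocol article, Statistical analysis, describes the diary work as follows: "We will also explore within-person associations between yoga practice, outcomes (pain, fatigue, mood) and mediators (pain catastrophizing, pain acceptance"), "among participants in the yoga condition". The models are multilevel random effects models with individuals' "mean levels of yoga practice as a control variable" and "practice rates person-centered to control for potentially spurious within-person associations". The same paragraph adds: "Multilevel models also enable strict control for potential confounds, such as serial autocorrelation in measurements".

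The data come from the intervention period: "participants will complete brief daily diaries on alternate weeks (4 weeks total").

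Two other places say what the analysis is for. Study Design presents the daily measures as an innovative feature that allows a rigorous test of pain catastrophizing and pain acceptance as mediators. The Discussion promises "the first systematic evaluation of the psychological mechanisms by which a yoga intervention may produce pain relief".

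Adherence and retention strategies lists, among the obstacles to attending sessions in this population, "unpredictable worsening of symptoms, limited energy, and alternate patient priorities given shortened life expectancies".

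**The concern.** The reason given for centring does not match what centring does. With the person mean in the model, the slope on centred practice compares a woman's days with her own other days. Stable differences between women, such as fitter women practising more, drop out. Anything that varies from day to day within a woman and moves with both practice and symptoms stays in. That remainder is exactly what a spurious within-person association is, and the sentence says centring controls it.

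Two such sources are plausible here. Symptoms may change practice on the same day, in either direction. Practice and symptoms may also both drift over the 8 weeks. Because the analysis uses the yoga arm only, no randomised contrast protects it.

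At stake is the mechanism conclusion. A negative practice-pain slope looks the same whether practice eases pain or pain stops practice. A flat slope could be a real benefit cancelled by women practising more on bad days.

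**Working it through.** The article gives no effect size, power or error rate for the diary models, so there is no figure to reproduce. The check is what a centred model returns when practice truly does nothing.

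**Inputs from the article.** About 65 women randomised 2:1, so 65 x 2/3 = 43 in the yoga arm. Four diary weeks, so 4 x 7 = 28 days. Symptoms are single items scored 0-9.

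**Assumptions, because the article does not give these values.** Within- and between-woman SD 1.5 points each, daily autocorrelation 0.4, practice recorded as yes/no each day, no missing diaries, two-sided 5% tests, same-day practice as predictor. The article states neither a same-day nor a lagged predictor.

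**Size by hand.** Let k be the change in log-odds of practice per symptom point and s the within-woman SD. The within-woman covariance of practice and symptom is about k x p(1-p) x s², and the variance of practice is p(1-p), so the spurious slope is about k x s². For k = -0.2 this is -0.2 x 1.5² = -0.45 points. The same k as an odds ratio per SD is exp(-0.2 x 1.5) = exp(-0.3) = 0.74.

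**Simulation, 1000 runs per row, true effect zero.** Each cell gives the slope and the share of trials significant.

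| Scenario | Centred only | Centred, autocorrelation modelled |
|---|---|---|
| No confounding | 0.00; 4.7% | 0.00; 4.6% |
| Stable between-woman confounding only | 0.00; 4.8% | 0.00; 5.7% |
| Bad days reduce practice, OR 0.90 per SD | -0.14; 30% | -0.11; 24% |
| Same, OR 0.74 | -0.43; 99% | -0.33; 97% |
| Same, OR 0.61 | -0.69; 100% | -0.54; 100% |
| Drift only: symptom -1 point, practice log-odds +1 | -0.08; 12.5% | -0.03; 6.1% |
| Drift only: symptom -1.5, log-odds +2 | -0.26; 70% | -0.11; 23% |

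Row two shows centring doing its real job. Rows three to five show what it leaves behind. Adding a study-day term to the autocorrelation model brings the drift rows to 4.2% and 4.6%, but leaves the OR 0.74 row at 97%.

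**Opposite direction.** With k = +0.2 the same-day slope is about +0.43. If the two effects add, a true benefit of 0.50 points would appear as about -0.50 + 0.43 = -0.07.

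**What a lagged model does.** Regress today's symptom on yesterday's practice, adjusted for yesterday's symptom and study day. Under a true zero effect this gave 4.0% to 5.3% significant in every scenario, with slopes within 0.01 of zero. Under a true same-day effect b it misleads. Write y(t) = b x(t) + e(t) and e(t) = r e(t-1) + noise. Substituting for e(t-1):

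y(t) = b x(t) + r y(t-1) - r b x(t-1) + noise.

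Yesterday's practice therefore has coefficient -r x b. With r = 0.4 and b = -0.5 this is +0.20. Simulation gave +0.19, significantly positive in 46% of trials and significantly negative in 0%. A real benefit would look like next-day harm.

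**The case against.** **Silence in a condensed article.** The article gives no model equation, and a lag or a week term may be in the full protocol or analysis plan. A reader might infer that the trial has no such terms; the document does not support that, and their absence from the article is not the point. What stands is the stated purpose of centring, which no further detail would make true.

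**A charitable reading.** Paired with the person mean, centring does stop between-woman differences from contaminating the within-woman slope, and this may be what was meant. If so, the remedy is the same rewording.

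**Other safeguards.** Centring is not the only one named: the person mean and serial autocorrelation appear too, and the latter is given only as an example. Modelling autocorrelation does more than correct standard errors, since it moved the slope from -0.43 to -0.33. It did not remove the bias.

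**Exploratory status.** The section speaks of exploring associations and does not say that practice relieves pain. That limits the harm. It does not dispose of the point, because Study Design and the Discussion claim a mediator test and an evaluation of mechanisms from the same data.

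**Direction of bias.** A reader might infer that the model is bound to show a false benefit. The document does not support this. The listed obstacles concern session attendance, and carrying them to home practice is an inference. Under Mindful Yoga Program, women are also taught to apply practice to pain as it occurs, so bad days could increase practice. This objection stands: the sign of the bias is unknown.

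**Conclusion.** The stated rationale is wrong: centring with the person mean controls stable between-woman confounding, not spurious within-woman associations. A same-day diary association therefore cannot support the mediator and mechanism claims. Under the assumed SD and autocorrelation, a change of 0.2 in the log-odds of practice per pain point is enough for a spurious slope of about 0.43 points in either direction. Even an odds ratio of 0.90 per SD gives 24% to 30% false positives. These sizes depend on the assumed values; that centring leaves the bias in place does not.

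The time-course part is the weaker half. It needs practice and symptoms both to drift, its sign depends on the directions of drift, and a mild drift falls to 6.1% false positives once autocorrelation is modelled.

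A reader might extend the doubt to the trial as a whole. The documents do not support that: the feasibility and acceptability outcomes and the randomised comparison do not use this model.

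**What to change.** 1. Reword the Statistical analysis sentence to say that centring, with the person mean in the model, removes between-person confounding.
2. Add study day or week to the diary models.
3. Report the same-day association together with lagged models in both directions: yesterday's practice to today's symptom, and yesterday's symptom to today's practice. Adjust each for the prior-day value of its own outcome, and use consecutive days within diary weeks.
4. Describe the results as associations without established causal direction, and limit the mediator and mechanism wording in Study Design and the Discussion to match.

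Do not make the lagged model the sole main analysis. It targets next-day carry-over, which is a different question, and a true same-day effect gives it the opposite sign. Neither form removes unmeasured causes that change from day to day, which is why the fourth change is needed as well as the third.

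Cost: no new data and a little more analysis. The lagged models lose the first day of each diary week, leaving 4 x 6 = 24 day-pairs per woman instead of 28 days. The mechanism claim becomes more modest.

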## Discussion

In this report we have summarized the challenges of designing a randomized controlled trial of a yoga intervention for metastatic breast cancer patients with long-term follow-up. The challenges we faced in this design included ensuring adequate recruitment including of minorities, limiting and controlling for selection bias, tailoring of the yoga intervention, and maximizing adherence and retention. This project will provide important information regarding the feasibility and acceptability of yoga as an intervention for women with advanced cancer, and valuable preliminary data on the psychological and functional effects of yoga for MBC patients, including the first systematic evaluation of the psychological mechanisms by which a yoga intervention may produce pain relief. This investigation will also establish rigorous methods for future research for testing the mechanisms by which yoga may affect pain, fatigue, emotional distress, and functional capacity in this population.

## Abbreviations

CONSORT: Consolidation of Standards for Reporting Trials
CPAQ: Chronic Pain Acceptance Questionnaire
ECOG: Eastern Cooperative Oncology Group
FFMQ-SF: Five Facet Mindfulness Questionnaire-Short Form
HADS: Hospital Anxiety and Depression Scale
IRB: Institutional Review Board
KPS: Karnofsky Performance Status
MBC: Metastatic breast cancer
RCT: Randomized controlled trial
